# INTRODUCTION

## BACKGROUND

Short bowel syndrome (SBS) is a rare condition included in The National Organization for Rare Disorders (NORD) database. The estimated prevalence of SBS in adults in the US is reported to be approximately 10,000-20,000 individuals (Oley Foundation [www.oley.org]; Short Bowel Syndrome Foundation [http://www.shortbowelfoundation.org]), affecting males and females in equal numbers. The disorder has numerous causes, both congenital and acquired, but a common etiological factor is the functional or anatomical loss of extensive segments of the small intestine, leading to a severe decrease in intestinal absorptive capacity. In children, the most common causes are necrotizing enterocolitis, intestinal atresias, and intestinal volvulus.^1^

The link between intestinal loss of the small bowel and the risk of SBS is self-evident. Losing large amounts of the small intestine compromises the digestive and absorptive processes. Adequate digestion and absorption cannot take place and proper nutritional status cannot be maintained. Treatment of SBS is focused on supplying the nutrients and vitamins that patients lack and may include (1) a high-calorie diet that includes vitamins, minerals, carbohydrates, proteins, and fats; (2) injections of vitamins and minerals; (3) administration of drugs that slow down the normal movement of the small intestine; and (4) feeding through a vein (i.e., parenteral nutrition (PN)).

Most SBS patients are initially fed with PN. In some patients, intestinal adaptation, alone or in combination with dietary modifications, allows weaning from PN. Unfortunately, many patients cannot be weaned from PN because of dramatically reduced intestinal length or function. Patients on long-term PN frequently experience serious metabolic complications. Most complications are hepatic and biliary disorders manifested by hepatic steatosis, fibrosis and cholestasis.[^1^](#_REFERENCES) These disorders can progress to fulminant liver failure.[^1^](#_REFERENCES) Before 2006, advanced liver disease was the most common cause of death in SBS patients.[^2^](#_REFERENCES) In infants with SBS, PN-associated liver disease (PNALD) is estimated to occur in 40-60% of those receiving long-term PN[^3,4^](#_REFERENCES) with mortality estimated to be as high as 80%.[^5,6,7^](#_REFERENCES)

Many consider PNALD to be caused in part by the intravenous lipid emulsions used to provide fat calories in the PN formulation, although the etiology is unclear.[^3,4,8^](#_REFERENCES) It has been suggested that PNALD may be caused by inflammation that is related to the type of intravenous lipid emulsion used.[^4,8^](#_REFERENCES) These fat emulsions cannot be eliminated from PN because by doing so would lead to the development of essential fatty acid deficiency and its concomitant complications.[^8,9^](#_REFERENCES) Recent data has shown that the replacement of a primarily omega-6 soybean oil lipid emulsion with those comprised primarily of omega-3 fatty acids may lead to reduction or avoidance of PNALD without predisposing the patient to essential fatty acid deficiency.[^3,10^](#_REFERENCES) Moreover, having a more bioavailable form of essential fatty acids that can be administered enterally may reduce or avoid the need for intravenous lipid emulsions entirely.

Although increased and earlier enteral feeding may reverse PNALD, data suggests that duration of hepatic dysfunction can last for several months after cessation of PN.[^11,12,13^](#_REFERENCES) In one retrospective study, children with a history of PNALD who have achieved PN independence had persistent alanine aminotransferase (ALT) elevations despite normalization of direct bilirubin concentrations. This suggests that hepatic injury may be ongoing beyond the time of bilirubin normalization.[^13^](#_REFERENCES) PN-dependent infants can achieve normalization of marked hyperbilirubinemia with enteral nutrition, however this improvement in liver function usually begins only after full enteral nutrition is tolerated and PN is withdrawn. These findings support the aggressive weaning of PN to enteral nutrition in infants with SBS. ^12^

Enterally administered long chain triglycerides in patients with SBS, especially those with hepatic dysfunction, are not well tolerated due to bile acid malabsorption, which leads to decreased micelle formation and fat digestion. Switching to other forms of fat such as medium-chain triglycerides that do not require micelles for absorption may be better tolerated in patients with bile acid or pancreatic insufficiency but are not optimal as they increase the osmotic load in the intestine. This may increase the chance of dumping; moreover, medium chain fatty acids do not contain essential fatty acids. The ability to provide the essential fatty acids such as those present in enteral formulas in a form that does not require the formation of micelles for absorption, would allow patients with SBS and those who are no longer PN dependent to receive adequate nutrition and continue to maintain the same growth trajectory as when they received the majority of their nutrition parenterally.

For example, enteral fish oil has been tried with limited success as an alternative to intravenous fish oil lipid emulsions in PN dependent infants with PNALD.^14^ In that case series, patients received a variety of products at various doses and actual absorption of the products was not determined. The results were further confounded by a variety of enteral feeding practices. Thus, no firm conclusions could be drawn from this retrospective study. In addition to improved hepatic function, early enteral fish oil administration may improve intestinal adaptation in infants with an enterostomy. Yang et al. have described how infants less than 2 months of age with an enterostomy who were tolerating some enteral nutrition (approximately 20 ml/kg/day) in combination with PN were shown to have increased enteral intake, better enteral protein absorption, decreased need for parenteral fat emulsions, and reduced conjugated bilirubin before reanastomosis and improved growth after reanastomosis.^15,16,17^ Furthermore, by improving tolerance of enteral feedings, bile flow can be stimulated and enterohepatic recirculation can be improved, such that PNALD can be prevented or reversed. Despite these findings, PN duration remained unchanged and actual fat reduction was more likely due to increased fat intake in the intervention arm and not due to improved absorptive capacity.

It is hypothesized that by using an external lipase device enteral nutrition will be better absorbed, and PN dependence will be reduced as enteral autonomy is increased. As mentioned previously, the goal of therapy for patients with SBS is to transition from parenteral nutrition to enteral nutrition. In one retrospective review conducted on infants at our institution's Short Bowel Syndrome Clinic from 1999 to 2004, the benefit of stopping PN and achieving enteral autonomy was demonstrated.^12^ Inclusion criteria included PN use for more than 1 month, serum direct bilirubin more than 3 mg/dL while on PN, and tolerance of full enteral nutrition with eventual discontinuation of PN. Twelve infants were identified with a PN duration of 5±1 months. Five patients underwent liver biopsy while on PN, and histological evidence of cholestasis was found on all specimens. Peak total and direct bilirubin levels were 10.5±1.9 and 7.0±1.6 mg/dL, respectively, and occurred at time of PN discontinuation. Only 2 patients had improvement in serum bilirubin levels before initiation of full enteral nutrition. After initiation of full enteral nutrition and discontinuation of PN, all patients achieved permanent normalization of bilirubin levels by 4 months (*P* < 0.05) after a 1-month plateau phase. Alkaline phosphatase levels approached reference range within this time but were not significant.

One of the challenges in providing enteral nutrition to patients with SBS is ensuring that the nutrition is adequately absorbed to achieve adequate growth and avoidance of deficiencies. The small intestine is the primary site of nutrient absorption; a decrease in absorptive capacity of nutrients in the small intestine may similarly impact the drug absorption process.

Alcresta Pharmaceuticals has developed a device which will assist in the absorption of enterally administered nutrition. RELiZORB is a single-use, point-of-care digestive enzyme cartridge that connects in-line with existing enteral feeding pump tubing sets and patient extension sets or enteral feeding tubes. RELiZORB is designed to hydrolyze (digest) fats contained in enteral formulas, mimicking the function of the digestive enzyme lipase that is normally secreted by the pancreas, the body’s digestive organ. By hydrolyzing (digesting) fats from enteral formulas, RELiZORB allows for the delivery of absorbable fatty acids and monoglycerides to patients. By virtue of its formulation and mechanism of action, it is hypothesized that RELiZORB will increase fatty acid absorption in patients with SBS and allow patients to achieve the same growth as that experienced while receiving parenteral nutrition. RELiZORB is therefore expected to increase intestinal nutrient absorption in SBS patients.

RELiZORB contains the digestive enzyme lipase bound to beads (iLipase®). Like human pancreatic lipase, the lipase in RELiZORB has sn-1, sn-3 selectivity in the hydrolysis of triglyceride fats. When enteral formula flows through RELiZORB, the lipase bound to the beads hydrolyzes fats in their triglyceride form, including important long-chain polyunsaturated fats (LCPUFAs), releasing omega-3 (docosahexaenoic acid (DHA) and eicosapentaenoic acid (EPA)) and omega-6 (linoleic acid (LA) and arachidonic acid (ARA)) into their absorbable fatty acid and monoglyceride forms. The iLipase® is retained within the RELiZORB cartridge by two filters as enteral formula flows through RELiZORB.

Figure 1. Hydrolysis of fat by lipase into monoglyceride and free fatty acids

[figure not shown]

Medications that have been used to manage SBS include teduglutide, a form of glucagon-like peptide 2, which is a protein involved in the adaptation and rehabilitation of the lining (mucosa) of the intestines, and somatropin (rDNA origin) for injection, a human growth hormone, thought to improve the ability of the small intestine to absorb nutrients, thereby lessening the need for PN. Both of these therapies are not without risk. Teduglutide carries a risk for acceleration of neoplastic growth whereas somatropin use has been associated with an increased risk of mortality. There is a need for a less toxic therapy.

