## SECONDARY OBJECTIVE

- To determine the effectiveness of the RELiZORB enzyme cartridge on the absorption of enteral nutrition when used daily for a total 90 days of treatment, in pediatric subjects with SBS who are PN dependent, aged 2 years – 18 years, by measuring the change in body weight (weight-for-age z-score) from baseline, assessed weekly throughout the study.

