## DROPOUTS

Subjects who are enrolled but do not receive the RELiZORB enzyme cartridge will be considered dropouts. Furthermore, enrolled subjects who receive the RELiZORB enzyme cartridge and do not complete any study assessments through Day 90 will be considered dropouts. Dropouts will be replaced in order to reach the goal of 32 subjects with evaluable data. Patients with at least one post-baseline study assessment will be retained for analysis.

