### Outcomes Evaluation

Continuous outcomes, which include all outcomes except the incidence of adverse events (AEs) and incidence of weaning from PN, will be described as indicated in the general overview above using summary measures at each visit. Incidence of ever weaning from PN will be summarized by frequency count and percentage. Analysis for incidence of AEs grade 2 or higher is described in the Safety Analysis section below.

Assessment of change in continuous outcomes will be made using the area under the curve between study day 7 and 90 (AUC_7-90_), adjusted for baseline, calculated over all relevant assessment timepoints (5 and 13 post-baseline weekly assessments for measurements obtained in clinic and at home, respectively). Measurements obtained in clinic will be assessed at study days 7, 14, 28, 60 and 90, while those obtained at home will be assessed on study days 7, 14, 21, 28, 35, 42, 49, 56, 63, 70, 77, 84, 90.

Adjustment for baseline will be made by dividing the outcome value at each assessment by the baseline value, leading to interpretation of AUC_7-90_ as a mean relative percent increase or decrease in outcome depending on whether AUC_7-90_ is greater or less than unity (1), respectively. AUC_7-90_ will be calculated as a time-weighted average, given by the equation:

$$\frac{0.5\cdot\sum\left( t_{i+1}-t_{i} \right)\left( r_{i}+r_{i+1} \right)}{\sum\left( t_{i+1}-t_{i} \right)}$$

where $t_{i}$ denotes the assessment day as described above,, and $r_{i}= y_{i}/y_{1}$ denotes the outcome at assessment day $t_{i}$ divided by the baseline (day 1) value. Hypothetical examples for a single subject with reduction in outcome at each visit is shown below in Figure 3 for measurements obtained in clinic (a) and measurements obtained at home (b). The dotted lines enclose a reference AUC_7-90_=1 (indicating no change in outcome), and the gray shaded area indicates AUC_7-90_.

Figure 3. Hypothetical examples of area under the curve for one subject

| [figure not shown] | [figure not shown] |
| --- | --- |
| a. Example of in-clinic outcome assessment. | b. Example of at-home outcome assessment. |

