A reliable estimate for the standard deviation (SD) of AUC_7-90_ for the primary outcome in this patient population is unavailable. Unpublished data for 7 patients are available, but at least 4 of these would not meet the eligibility criteria for this study (ages 1-10; 1 had a STEP procedure; 3 have pancreatic involvement). Nevertheless, the mean±SD reduction (AUC_7-90_) for these 7 patients was 0.81±0.14, representing a 19% decrease over 90 days. Using this SD with a sample size of n=32, a 20% observed reduction in outcome would provide a 95% confidence interval (CI) = (0.75, 0.85), ruling out a true mean population reduction smaller than 15%. Conservatively, if the SD was doubled (SD=0.28), the 95% CI = (0.7, 0.9), excluding a true mean population reduction smaller than 10%, our target threshold In general, for any continuous outcome, a sample size of n=32 with two-side alpha=0.05 will provide 80% power to detect an effect size (mean/SD) as small as 0.51, considered a medium-sized effect^25^.

Dichotomous outcomes and will be presented as proportions. The variance for a proportion (p) is at a maximum, and its CI at its widest, when p=0.50. Proportions farther from 0.50 (in either direction) have smaller variances, and hence narrower CIs. A range of proportions with 95% CIs for a sample of 32 subjects is provided; small: p=0.20 (0.06 – 0.34); medium: p=0.50 (0.33 – 0.67); and large: p=0.80 (0.66 – 0.94).

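### Growth z-scores are assessed by the baseline-ratio Day 7-90 time average designed for PN calories, which measures average level rather than growth trajectory and misreads zero or negative baselines

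*Protocol*

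**What the plan says.** Section 1.1 (Background) frames growth as something followed over time. Patients should "continue to maintain the same growth trajectory as when they received the majority of their nutrition parenterally", and the device is expected to "allow patients to achieve the same growth as that experienced while receiving parenteral nutrition". Section 2.2 makes weight the only secondary efficacy outcome, "by measuring the change in body weight (weight-for-age z-score) from baseline, assessed weekly throughout the study". Height, head-circumference and BMI z-scores are exploratory endpoints (3.3.4).

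Section 10.2.2 applies one measure of change to every continuous outcome, so it covers all of these. Each value is divided by the Day 1 value, and "AUC_7-90_ will be calculated as a time-weighted average, given by the equation" that follows in that section. The result is read as a relative increase or decrease according to whether it lies above or below 1. Clinic measurements use Days 7, 14, 28, 60 and 90; home measurements use 13 days from 7 to 90. The same section also promises descriptive summaries at each visit.

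Section 10.2.5 rests the sample size on PN calories. It adds a general statement for continuous outcomes: "a sample size of n=32 with two-side alpha=0.05" "will provide 80% power to detect an effect size (mean/SD) as small as 0.51". It gives no SD, target or test for growth.

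**The concern.** A time average suits PN calories, where total exposure over the period is of interest. Growth accumulates: a change in growth rate appears as a drift in z-score that is largest at the end. Averaging from Day 7 to Day 90 blends that drift with visits at which little of it has occurred, so the reported figure is neither a rate nor the change reached by Day 90. A reader who takes it as the 90-day growth effect will understate a gradual or late gain or loss.

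The division by baseline adds a second difficulty. A z-score has no natural zero point that makes ratios meaningful, and it can be zero or negative. At stake is the interpretation, and in some circumstances the precision, of the secondary outcome and several exploratory ones. The primary outcome is not affected.

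**Working it through.** **Plan's own figures.** For a one-sample t-test with n = 32 and two-sided alpha 0.05 (noncentral t, 31 df), the effect size detectable with 80% power is 0.511, and power at 0.51 is 79.8%. The intervals 0.80 ± t × SD/√32 are (0.750, 0.850) for SD 0.14 and (0.699, 0.901) for SD 0.28. All agree with 10.2.5. The 0.14 belongs to PN calories: "the mean±SD reduction (AUC_7-90_) for these 7 patients was 0.81±0.14". The calculations below use n = 32 because section 3.4 says "Dropouts will be replaced in order to reach the goal of 32 subjects with evaluable data".

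**Weights in the average.** The trapezoid rule in 10.2.2 gives 0.042, 0.127, 0.277, 0.373 and 0.181 on the clinic grid. On the weekly grid Day 90 carries 0.036. Day 28 onward carries 83.1% (clinic) and 78.9% (weekly).

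**Share of the Day 90 change kept, difference scale.** The share is the sum of weight × fraction of the Day 90 change reached at that visit.
- Linear from Day 1: the mean day is (7 + 90)/2 = 48.5, so the share is (48.5 − 1)/89 = 0.534 on both grids.
- Start at Day 45: clinic 0.373 × 15/45 + 0.181 = 0.305; weekly 0.273.
- Linear to a plateau at Day 28: the Day 7 value is 6/27 = 0.222, so (21/83) × (0.222 + 1)/2 + 62/83 = 0.902 on both grids.
- Step complete by Day 7: 1.00.

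**Precision against a slope.** The protocol gives no growth variances, so these are assumptions: m = mean Day 90 change, b = between-child SD of that change, e = measurement SD, independent between visits. Each child's curve is taken as proportional to the common shape. Then

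effect size = m·k / √(b²k² + e²q²),

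where k is the share kept and q the noise multiplier. For average minus baseline, q is 1.125 (clinic) and 1.039 (weekly). For Day 90 minus baseline it is 1.414. For the least-squares slope over the 89 days from Day 1 to Day 90 it is 1.143 and 0.850. Power is from the noncentral t.

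Height z on the clinic grid, assumed m = 0.08, b = 0.08, e = 0.10, linear change:
- Average: 0.0427/√(0.0427² + 0.1125²) = 0.355, power 49%.
- Day 90 change: 0.08/√(0.08² + 0.1414²) = 0.492, power 77%.
- Slope: 0.08/√(0.08² + 0.1143²) = 0.573, power 88%.

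The same formula for the other cases, including weekly weight z with assumed m = 0.10, b = 0.25:

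| Case | Average | Day 90 | Slope |
|---|---|---|---|
| Height, linear | 49% | 77% | 88% |
| Height, plateau by Day 28 | 84.0% | 77.0% | 84.4% |
| Weight, e = 0.11, linear | 38% | 46% | 54% |
| Weight, e = 0.11, plateau by Day 28 | 49.8% | 46.1% | 50.8% |
| Weight, e = 0.05, linear | 53% | 56% | 58% |
| Weight, e = 0.02, linear | 58% | 59% | 59% |

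For an immediate step the order reverses. On the clinic grid the mean day is 200/6 = 33.3 and the sum of squared deviations is 6063, so the slope keeps (33.3 − 1) × 89/6063 = 0.475 of a step. Under the height assumptions its effect size is 0.038/√(0.038² + 0.1143²) = 0.315 (power 41%). The average has 0.08/√(0.08² + 0.1125²) = 0.579 (power 89%).

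**The ratio as written.** For a linear gain of 0.3 z by Day 90 from baseline z₀, the result is 1 + 0.3 × 0.534/z₀:

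| z₀ | Ratio average |
|---|---|
| +1 | 1.16 |
| +0.1 | 2.60 |
| 0 | undefined |
| −0.1 | −0.60 |
| −1 | 0.84 |

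The same gain reads as an increase, a decrease or a negative number depending only on the starting point. Two children at +1 and −1 who both gain 0.3 average (1.16 + 0.84)/2 = 1.00, which the plan would read as no change.

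**The case against.** The strongest reply is that the growth analysis is descriptive and already shows what matters. Section 10.2.2 summarizes each outcome at every visit, so Day 90 z-scores will be reported. Section 10.2.1 adds by-subject summaries and profile plots. Under section 5.0, feeding is adjusted to keep children on their growth trend, with weekly review. The hypothesis is maintenance, and a z-score is already age-referenced: if nothing changes, there is nothing to attenuate. All of this stands and limits the consequence. It does not make the prescribed measure of change fit the question, because the visit summaries describe levels while assessment of change is assigned to the ratio average.

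Several stronger readings are tempting, and the documents do not support them.
- That the average halves any growth change: 53% holds only for linear change.
- That early visits dominate: Day 28 onward carries 79-83% of the weight.
- That power is necessarily lost: attenuation shrinks the SD as well as the mean, and the comparison turns on assumed variances and curve shape.
- That a stated power figure fails: none is stated for growth.
- That a fall in growth during PN weaning would probably be missed: the visit summaries and weekly weight review argue against it.

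The shares and powers above are also for average minus baseline. They do not describe the ratio the protocol writes, whose fault is different.

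**Conclusion.** The point holds as a mismatch between summary and question, worth correcting because the correction is cheap. The Background sentences are sound; the text to change is 10.2.2.

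On a difference scale, the share of the Day 90 change kept runs from about 27% to 100% across the shapes tried. The precision loss against a slope is material when measurement error is large relative to true between-child variation and change is gradual or late. It is negligible when measurement error is small and change is gradual, or when change plateaus by Day 28. It is reversed for an immediate step. These are ranges under assumed growth means and SDs, not estimates for this trial.

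The ratio defect needs no such assumptions: it follows from the formula and the z-score scale. The effect is confined to one secondary and several exploratory outcomes.

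**What to change.** In 10.2.2, for weight-, height-, head-circumference- and BMI-for-age z-scores only, replace the ratio AUC7-90 with each child's least-squares slope of raw z-score on actual study day, using baseline and all follow-up values. Express it as z-score change per 90 days, with mean and 95% CI. Report Day 90 minus baseline z-score beside it as a check on linearity. Keep AUC7-90 for PN calories. Moving to Day 90 alone while keeping the division by baseline would not repair the growth analysis.

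The cost is analysis wording; the measurements are already scheduled. Growth outcomes would carry a different summary from PN calories. The slope also assumes roughly linear change over 90 days and would understate an abrupt early step, which the Day 90 difference would reveal.
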